#### Sociodemographic variables

We will register age (in years), parental level of education using mother and father’s job, region of origin (Swiss cantons and foreign countries), and migration status (type of residence permit). We will also ask participants whether they belong to a gender or sexual minority. We will use the Gender-Role Identity Scale (GRIS) [35], which has been validated in French. The GRIS uses 11 questions and covers three dimensions: sex assigned at birth and gender identity (questions 1 to 4, categorical items, will be reported as proportions), sexual orientation (item 5, will be reported as proportion), and gender roles and identity (questions 6 to 11, items 6 to 8 capturing masculinity and 9 to 11 femininity, combined into a single score ranging from − 2 (very feminine) to + 2 (very masculine), will be reported as mean scores) [35].

#### Educational trajectory

We will register participants’ highest level of educational attainment (type of school and grade), whether they dropped out of school, met serious school difficulties (not having the grades to pass the year, high number of absences (more than 100 periods per year), suspension days, accumulation of detention hours beyond what could be reasonably served during the academic year), had any stay in foster shelter or foster family, or had any stay in juvenile detention centres. These variables will be coded categorically, summarized as proportions.

#### Psychological and health-related variables

We will assess health literacy using the Health Literacy for School Aged Children (HLSAC-5) [36], which includes 5 questions assessed on a 4-point scale and has been validated in French [37]. A sum score ranging from 0 to 20 will be computed, and final score at *T*_0_, *T*_1_, and *T*_2_ will be used. We will ask the participants whether they have a diagnosis of a psychiatric disorder and whether they are currently taking medication for psychiatric problems. We will also ask the participants whether they have a diagnosis of a chronic condition. These variables will be coded categorically (yes/no). Adverse childhood experiences will be assessed with the Childhood Trauma Questionnaire Short Form (CTQ-SF), which includes 25 questions assessed on a 5-point scale [38]. A sum score (range 0–100) will be computed, and the final score at *T*_0_ will be used. It is well accepted by adolescents aged 14 or more [38] and has been validated in French [39]. We will also ask one question about the history of previous suicidal behaviours.

#### Study site information

Finally, we will collect the following information on study sites: canton, type of vulnerable population, clinical or community site, suicide-related routine care, and previous suicide prevention involvement. We will derive different categories for suicide-related routine care. The categorization will be developed by at least two project partners who are experts in suicide prevention. The interrater reliability will be tested with a kappa. The categorization will be trained until a kappa ≥ 0.7 is reached.

### Participant timeline {13}

Participants will be assessed at three time points: baseline (*T*_0_), 1 week post-baseline (*T*_1_), and 3 months post-baseline (*T*_2_). Participants will answer paper-based self-reported questionnaires at *T*_0_ and *T*_1_. At *T*_2_, they will answer orally during a phone call, or another preferred mean of communication. When needed (low ability to read/write), the study team will help the participant to complete the questionnaire. At T_0_, the assessment will be performed in groups, immediately followed by the intervention. At T_1_, the interviewer will approach participants at the study site. At *T*_2_, the interviewer will call or contact the participant using the selected alternative communication means. The questionnaire takes ~30 min at *T*_0_ and ~15 min at *T*_1_ and *T*_2_. To avoid loss to follow-up, the interviewer will contact participants who are unavailable at the study site for the *T*_1_ follow-up assessment to complete the questionnaire by offering alternatives such as in-person appointment or phone call.

Participants will receive financial compensation for their participation (a total of CHF 80—vouchers). They will receive CHF 20—after the baseline assessment, CHF 20—after the 1-week assessment, and CHF 40—after the 3-month assessment. Figure 1 provides details on the schedule of enrolment, intervention, assessments, and incentives.

**Fig. 1 Fig1:**
[figure not shown]
Timeline of enrolment, interventions, assessments, and incentives as per SPIRIT guidelines. ^1^Primary outcome. ^2^Secondary outcome. *Max. 1-month post-*T*_0_. The Standard Protocol Items: Recommendations for Interventional Trials (SPIRIT) Guidelines can be found at https://spirit-statement.org/publications-downloads/

### Sample size {14}

Estimates for the sample size calculation (means, standard deviations, intraclass correlation, and effect size) are based on the results of the previous trial conducted with the same intervention in adolescents in Swiss secondary schools [19]. To estimate the effect size, we used data from the intervention group (*n* = 201 who participated at baseline and follow-up). This choice was driven by the significantly higher scores at baseline in the control group compared to the intervention group. The scores of the control group remained stable over time (mean = 23 at baseline and follow-up). The scores of the intervention group were lower at baseline but increased over time (mean = 21 at baseline and 24 at follow-up, sd = 6). This three-point difference on the 0–36 point scale was used as the effect size. The expected cluster size and cluster variability are based on the expected group sizes at the study sites (from 5 to 15 participants, with an average of 10 participants). With alpha = 0.05, power = 0.80, a two-sided test, an expected cluster size *k* = 10, variation coefficient (variation in the cluster size) = 0.5 (5 to 15 adolescents per cluster), ratio cluster = 1:1, intraclass correlation = 0.05, mean = 21 in the intervention group (standard deviation = 6), and mean = 24 in the control group (standard deviation = 6), we need *k* = 20 and *n* = 200. To account for attrition, we increased the sample size by 20% (*k* = 24, *n* = 240). Even though the study is a superiority RCT, we used a two-sided test of the difference between groups, to provide a conservative sample size, in line with the recommendations of Good Clinical Practice (GCP). The sample size was computed with Stata 18 using a test to compare two independent means in a cluster-randomized design.

### Recruitment {15}

The project will run for 4 years, from October 2024 to September 2028. Data collection will take place between January 2025 and June 2027.

### Assignment of interventions: allocation

#### Sequence generation {16a}

Participants will be assigned to a group, and the group will be randomized to an intervention or control condition. Clusters will be randomized, using a 1:1 randomization with a stratification on the study sites. A random computer-generated allocation will be used in each study site, with block = 2.

#### Concealment mechanism {16b}

Clusters will be randomized using sequentially numbered, opaque, sealed envelopes. They will be opened once the creation of a group is confirmed.

#### Implementation {16c}

The Clinical Trial Unit of the Faculty of Medicine at the University of Bern will create confidential randomization lists for each site.

#### Who will be blinded {17a}

This is an open-label trial. The participants and the study team will not be blinded to their study group, as the intervention consists of scheduled workshops whose organization requires direct coordination with the study team.

#### Procedure for unblinding if needed {17b}

Unblinding will not occur, as it is an open-label study.

### Data collection and management

#### Plans for assessment and collection of outcomes {18a}

A detailed description of the instruments, including measures of validity and reliability, is provided in the ‘Outcomes {12}’ subsection. Data will be collected on paper forms at baseline and *T*_1_. Data will be entered directly into REDCap® at *T*_2_ and at *T*_1_ if this visit occurs over the phone. Data collection and extraction from the REDCap® electronic database will be carried out by trained team members. Central data monitoring will be performed through programmed checks. All source documents, including demographic data, randomization number, informed consent forms, visit dates, paper questionnaires, adverse and serious adverse events reports, will be stored in a closed cupboard at the Sponsor-Investigator’s office at the University of Lausanne for the duration of the project.

#### Plans to promote participant retention and complete follow-up {18b}

See the ‘Criteria for discontinuation or modification of assigned interventions {11b}’ and ‘Strategies to improve adherence to interventions {11c}’ subsections.

#### Data management {19}

REDCap®, a GCP-compliant online data management system, will be used to manage the collected data. This system allows the differentiation of each study team member and their function by providing personal identification for each user. Other functionalities include data security, monitoring, and automated reporting. The data will be managed and monitored by the interviewers under the supervision of [name], an expert in clinical trials, who will be responsible for central data monitoring for the study duration. Monitoring visits will be organized by the Clinical Trial Unit of the University of Bern.

All study data are archived for 10 years after study termination or premature termination of the study. During the study, the identification lists will be stored on the servers of the University of Lausanne. After completion of the data collection, the identification lists will be securely sent to the centres (CHUV, HUG, and Stop Suicide) for archiving on secure servers for 10 years and will be permanently deleted from the server of the University of Lausanne. Further use of the study data is detailed in the ‘Confidentiality {27}’ subsection.

#### Confidentiality {27}

Direct access to source documents will be permitted for purposes of monitoring, audits, and inspections. A restricted number of persons (investigators and interviewers) will have access to the participants’ personal details, using unique and persistent identifiers. To ensure confidentiality, this electronic list will be kept in a separate file protected by a password.

Data will be stored on the secure servers at the University of Lausanne during the project. They will be shared with the research team via electronic files (.csv files). Data will be publicly available (although upon request). Only human subject data properly de-identified and prepared under applicable legal and ethical guidelines will be entered into the online database. Once the project is completed, data (dataset and documentation) will be archived and stored in an online repository (SwissDatabase). Data will be available on SWISSUbase, and its access will require approval from the Sponsor-Investigator. Identification lists will be available at the study site for 10 years.

#### Plans for collection, laboratory evaluation and storage of biological specimens for genetic or molecular analysis in this trial/future use {33}

No biological specimens will be collected.

## Statistical methods

### Statistical methods for primary and secondary outcomes {20a}

For all statistical analyses, we will use a two-sided *α* = 0.05. We will use a Bonferroni-Holms adjustment in case of multiple testing. As participants are clustered in groups, we will use mixed-effect models, with participants nested in clusters. Statistical software will include Stata 18 and R version 4 (or new versions of these statistical software). We will use intention-to-treat analyses. We do not plan interim analyses. The use of adjusted analyses improves precision and power and will be considered as primary analyses [40]. Any deviations from the original statistical plan will be described and justified in the final trial report.

As preliminary analyses, we will examine the distributional properties of the variables, correlations, and patterns of missing data. Then, we will test whether groups (intervention vs. control) are similar at baseline using bivariable associations for all baseline characteristics and the baseline level of outcome variables. We will use standardized mean differences to compare baseline characteristics between groups, with 0.1 being considered as the threshold for balance. No inferential tests are planned for these analyses.

#### O1–O2

We will use a mixed-effect linear regression model (or negative binomial model, according to the outcome’s distribution) to test whether the primary suicide prevention intervention (intervention vs. control) predicts the score of suicide awareness (PSAS-9) at *T*_1_ (O1) and *T*_2_ (O2). We will report unadjusted and adjusted regression models. The primary analysis will be the adjusted model, controlling for baseline characteristics and using multiple imputation by chained equations (MICE) for baseline missing values on covariates [41].

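### The primary model does not commit to the baseline PSAS-9 score or to study site, and it lets the observed distribution change the effect measure

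*Protocol article*

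**What the plan says.** All references are to the protocol article.

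- **Adjustment.** Section O1–O2 makes the adjusted model primary: "The primary analysis will be the adjusted model, controlling for baseline characteristics". No list follows. Section {20a} says that adjusted analyses were chosen for precision and power.
- **Vocabulary.** For the comparison of arms at baseline, section {20a} plans to proceed "using bivariable associations for all baseline characteristics and the baseline level of outcome variables", which names two items. The Outcomes section likewise describes the outcome scales first and then introduces a separate list of characteristics collected at T0. That list holds no outcome score.
- **Site.** Clusters are allocated "using a 1:1 randomization with a stratification on the study sites", in blocks of 2 (Sequence generation {16a}; also Trial design {8}). The model structure in {20a} is "mixed-effect models, with participants nested in clusters". No section enters site as a fixed or random effect. Section {11c} says that routine care, recorded per site, will be a covariate.
- **Model family.** Section O1–O2 plans a "mixed-effect linear regression model (or negative binomial model, according to the outcome", and the sentence goes on to make the outcome's distribution the criterion. O3–O6 follows the same scheme.
- **Sample size {14}.** "With alpha = 0.05, power = 0.80, a two-sided test", on a comparison of two means: "This three-point difference on the 0–36 point scale was used as the effect size".

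**The concern.** The primary outcome is the PSAS-9 score at T1, not a change score. A chance difference between arms at T0 therefore carries into the estimate unless the T0 score is in the model. The sponsor has met this before: the sample size section reports baseline means of 23 and 21 in the two arms of the earlier school trial, a gap of 2 points against a target effect of 3. If the T0–T1 correlation were 0.68 with equal SDs (an assumption), a 2-point gap would shift an unadjusted comparison by about 0.68 × 2 = 1.36 points.

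Site matters for a different reason. Randomising within site balances the arms across settings as different as detention centres and psychiatric care. If the model ignores site, differences between sites are counted as noise between groups, and the gain from stratifying does not reach the standard error.

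The choice of model family affects what is estimated. If it is made after the data are seen, the primary effect may be a difference in points or a ratio of means, and only the first was powered.

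**Working it through.** **1. The plan's own figure.** Inputs from Sample size {14}: difference 3, SD 6, two-sided alpha 0.05, power 0.80, mean cluster size 10, coefficient of variation 0.5, ICC 0.05.

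- Per arm without clustering: 2 × (6 × (1.960 + 0.842) / 3)² = 62.8.
- Design effect: 1 + ((0.5² + 1) × 10 − 1) × 0.05 = 1.575.
- 62.8 × 1.575 = 98.9 per arm, or 9.89 clusters, rounded up to 10. This gives k = 20 and n = 200, as stated; power at 200 is 0.804.

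The calculation has no term for baseline adjustment or for site.

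**2. Baseline score.** If T0 and T1 correlate at r, adjustment multiplies the standard error by √(1 − r²). The article gives no T0–T1 correlation. Its nearest figure is the test-retest correlation of 0.68 in the PSAS-9 description.

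| r (assumed) | 1 − r² | SE factor | SE smaller by | Power at n = 200 |
|---|---|---|---|---|
| 0.40 | 0.840 | 0.917 | 8% | 0.867 |
| 0.50 | 0.750 | 0.866 | 13% | 0.902 |
| 0.68 | 0.538 | 0.733 | 27% | 0.970 |

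The 27% needs r = 0.68 at both individual and cluster level. With 0.68 within clusters and a lower correlation r_b between cluster means, the variance ratio is [0.05(1 − r_b²) + 0.095 × 0.5376] / 0.145:

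- r_b = 0: 0.697, so the SE is 17% smaller.
- r_b = 0.5: 0.611, so the SE is 22% smaller.

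If other covariates already explain 10% or 30% of the variance, the further reduction from the T0 score is 1 − √(0.5376/0.9) = 23% or 1 − √(0.5376/0.7) = 12%.

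**3. Site.** Cluster-level simulation, 4,000 runs per scenario: 24 groups of 10 in 8 sites (2 or 4 groups per site, assumed; the article says at least 8 sites), blocks of 2, no attrition, no baseline adjustment, total ICC 0.05. The share of the ICC that lies between sites is unknown and was varied.

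| Site share of ICC | Model SE ÷ true SE, site omitted | Type I error, site omitted | Type I error, site fixed | Power for 3 points, omitted / fixed |
|---|---|---|---|---|
| 0 | 0.98 | 0.053 | 0.051 | 0.879 / 0.861 |
| half | 1.09 | 0.030 | 0.050 | 0.895 / 0.911 |
| all | 1.21 | 0.018 | 0.045 | 0.913 / 0.964 |

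Omitting site leaves the SE about right at one end and 21% too large at the other. The error is always in the conservative direction.

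**4. Model family.** The plan's means are 21 and 24 with SD 6. The upper limit of 36 lies (36 − 24)/6 = 2 SD above the higher mean, and a negative binomial model has no upper limit. On its scale the planned effect becomes 24/21 = 1.14. The same ratio applied to a mean of 28 would be 28 × 24/21 − 28 = 4 points, so the two models do not estimate the same quantity.

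**The case against.** The strongest reply is that the article is silent on the covariates and excludes nothing. A covariate list commonly sits in the statistical analysis plan, which is not shown; section {20c} says that plan will give analytical detail. The sentence on standardised differences in {20a} uses baseline characteristics alone where the sentence before it named two items, so the short phrase may cover both. The precision rationale also favours including the T0 score. On site, the T0 list ends with canton, type of vulnerable population, clinical or community setting, routine care and earlier prevention work, so site-level information may well enter the model.

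Much of this stands. A reader might infer that the T0 score is barred from the model; the text does not say so. A reader might also infer that the balance rule, "with 0.1 being considered as the threshold for balance", will select covariates. The article presents it as a descriptive check and never uses it that way, so no fault is found there.

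Two things remain. Site characteristics are coarser than the randomisation stratum, and the article does fix the nesting, without a site level. The linear-or-negative-binomial rule is stated in the text, so silence does not explain it.

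**Conclusion.** The point holds as a defect of wording in the primary model, and it should be corrected. The text does not commit to the T0 PSAS-9 score, does not include the stratification factor, and makes the primary effect measure depend on the observed data.

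The size rests on assumptions. Baseline adjustment would shrink the SE by about 8% to 27%; the upper figure takes a test-retest correlation as the T0–T1 correlation in a different population after an intervention. Leaving out site makes the SE 0% to 21% too large at a total ICC of 0.05, depending on an unknown site share.

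Two stronger readings are not supported. The trial is not shown to fall below its stated 80% power, because the sample size takes no credit for adjustment; what is forgone is available precision. Nor does omitting site invalidate the test: type I error falls below 5% when sites differ, and does not rise.

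**What to change.** - In O1–O2, state that PSAS-9 is analysed with a linear mixed model containing arm, the T0 PSAS-9 score and study site (fixed or random), with a random intercept for the randomised group. Delete the negative binomial alternative for this outcome.
- In O3–O6, name the T0 score of the same outcome and study site in the same way.
- Align {11c}, {20a} and O1–O2. If site is a fixed effect, drop routine care, which is constant within site and cannot be estimated alongside it.

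This is wording only; the T0 scores and site are already to be collected. The cost is degrees of freedom: with fixed site effects and no true site differences, power for 3 points in the simulation falls from 0.879 to 0.861. A random site effect reduces that loss.

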#### O3–O6

For the other secondary outcomes, knowledge on suicide (LOSS), knowledge of local resources, suicidal thoughts (SIDAS), and psychological distress (K-6), we will also use mixed-effect linear regression models (or negative binomial models, according to the outcome’s distribution) with the intervention as the predictor. The same unadjusted and adjusted analyses as described above will be used. Analyses for outcomes at *T*_1_ and *T*_2_ will be performed separately.

#### O7

To explore how many vulnerable adolescents previously accessed primary suicide prevention before the study, we will compute the proportion of access to primary suicide prevention along with 95% confidence intervals. We will also explore associations between access to primary suicide prevention and participants’ baseline characteristics using bivariable and multivariable mixed-effect logistic regression models.

#### O8

To explore the characteristics of missingness and attrition, we will analyse missingness and attrition by comparing the characteristics of respondents and missing/dropouts. We will use mixed-effect linear, negative binomial, and logistic regression models, depending on the variable’s distribution. We will also discuss effect sizes using relative bias [42].

#### Safety

We will calculate the percentage of SAEs, attempted suicides, and deaths by suicide separately in each group, with 95% confidence intervals. As the number of events will presumably be very low, no inferential test is planned. We will also use percentages with 95% confidence intervals for AEs. We will calculate mean scores of self-reported acceptability using standardized mean differences between the intervention and control groups.

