**Discussion:**

We expect that a brief primary suicide prevention intervention (psychoeducation) will be effective and safe in vulnerable adolescents.

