#### Safety outcomes

We will systematically record SAEs, including suicide attempts and deaths by suicide before the participants leave the study site and up to 1-month post-baseline. According to the Swiss legislation, a SAE is any adverse event that [1] results in death or is life-threatening, (2) requires inpatient hospitalization or prolongation of existing hospitalization, (3) results in persistent or significant disability or incapacity, or (4) results in a congenital anomaly or birth defect. An in-depth clinical assessment by psychiatrists with an expertise in suicidal behaviours will be conducted in case of suicide attempts or deaths by suicide to rule out or establish a possible link to the intervention. Other AEs include self-harming, insomnia, appetite problems, substance use, and para-suicidal endangerment behaviours, as identified and reported by the local team before the participants leave the study site and up to 1-month post-baseline. Proportions of participants with the respective (S)AEs will be reported. At T_1_, we will also record self-reported distress due to the intervention using two questions related to the distressing and pleasurable nature of the intervention on a scale from 0 to 4 [19, 25]. We will use a sum score at *T*_1_ as the safety outcome.

In addition, we will collect the relevant following characteristics at T_0_:

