#### Adverse event reporting and harms {22}

As the intervention has previously been shown as acceptable [19], we do not expect SAEs related to the study intervention. The potential discomfort created by the discussion of suicide will be handled by the psychologist, and information on local resources will be given to all participants. The study sites serve populations with high suicide risk. Suicide attempts and deaths by suicide may occur during the study period, as they do outside the study period in this population. The study sites have specific procedures for dealing with such events. In addition, we will train all staff at the study sites (e.g. medical, educational, prison staff). The intervention for the staff will be an awareness session (‘module de sensibilization’) of a standardized suicide prevention intervention for professionals given by suicide prevention experts (Groupe Romand Prévention Suicide, Stop Suicide, University of Lausanne) [46]. If a suicide attempt or a death by suicide occurs during the study period and up to 1-month post-baseline, contact will be made between the local professional team and the suicide prevention experts to determine which additional support is needed. Interventions include debriefing, group support, and specific postvention interventions for the youth and the professional team.

Several characteristics of the SAEs will be reported to the Sponsor-Investigator within 24 h, including time, duration, severity, and outcome of the event, action implemented, and link to the study participation. SAEs will be reported within 15 days to the Ethics Committee if it cannot be excluded that their occurrence is related to the ongoing study.

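### For serious and other adverse events the plan gives a percentage per arm but no between-arm estimate; a risk difference with a cluster-aware confidence interval should be added.

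*Protocol article*

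**What the plan says.** The Safety subsection of the statistical methods plans the "percentage of SAEs, attempted suicides, and deaths by suicide separately in each group, with 95% confidence intervals". It gives a reason for stopping there: "As the number of events will presumably be very low, no inferential test is planned". Other AEs follow: "We will also use percentages with 95% confidence intervals for AEs". No risk difference, risk ratio or other contrast between the arms is named for any of these events.

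Other safety-related measures are compared between arms. The same subsection plans "mean scores of self-reported acceptability using standardized mean differences between the intervention and control groups", and the Safety outcomes subsection designates this T1 sum score "as the safety outcome". Under O3–O6, SIDAS and K-6 are modelled with the intervention as predictor at T1 and T2.

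Three further places bear on the point:
- Adverse event reporting and harms {22} states: "Suicide attempts and deaths by suicide may occur during the study period, as they do outside the study period in this population".
- Methods for additional analyses {20b} repeats the primary, secondary and safety analyses by vulnerable group and by gender, to see whether the intervention's effect differs between them.
- The Discussion paragraph of the abstract expects that the intervention "will be effective and safe in vulnerable adolescents".

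**The concern.** If events occur in this population anyway, the percentage in the intervention arm mixes background with anything the workshop causes. The control arm, matched on duration, group size and format, supplies the background. The difference between the arms is therefore the quantity that bears on harm, and it is the one not planned for events.

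The stated reason supports a narrower decision than the one taken. Few events make a p-value uninformative. They do not make a difference with its confidence interval uninformative, because that interval shows how much excess harm the data leave open. The reason is also given for SAEs, suicide attempts and suicides. The document does not say that the other AEs (such as insomnia, appetite problems or substance use) will be rare, yet they receive the same treatment.

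The subgroup plan asks whether the intervention's effect on safety outcomes differs between subgroups, but for events no effect has been defined.

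At stake is what the report can say about safety. Two percentages side by side do not tell the reader what excess has been excluded, and neither does an absence of events.

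**Working it through.** **Inputs.** From Sample size {14}: 240 participants, mean cluster size m = 10, coefficient of variation of cluster size CV = 0.5, ICC = 0.05. From Sequence generation {16a}: 1:1 allocation. I take 120 per arm, all observed for events. The document gives no event rates, so every event count below is an assumption.

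**The plan's own figure.** For a 3-point difference with SD 6, two-sided alpha 0.05 and power 0.80, the individual-level requirement is 62.8 per arm. The design effect is 1 + [(1 + CV²)m − 1] × ICC = 1 + (12.5 − 1) × 0.05 = 1.575. Then 62.8 × 1.575 = 98.9 per arm, or 9.89 clusters of 10, rounded up to 10. This reproduces the stated 20 clusters and 200 participants, and 200 × 1.2 = 240. The protocol states no figure for safety.

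**Interval for the missing contrast.** With Wilson limits l and u in each arm and D = p1 − p2, the Newcombe interval runs from D − √[(p1 − l1)² + (u2 − p2)²] to D + √[(u1 − p1)² + (p2 − l2)²]. To allow for clustering I replace 120 by 120/1.575 = 76.2. This borrows the ICC of the primary outcome, which may not hold for events, so both versions are shown as a range.

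*No events in either arm.* The Wilson upper limit is z²/(n + z²).
- Ignoring clustering: 3.84/123.84 = 3.1%.
- With the design effect: 3.84/80.03 = 4.8%.

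The difference is then 0 with limits ±3.1 or ±4.8 points.

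*Six against three.* The planned output is 5.0% (Wilson 2.3 to 10.5) and 2.5% (0.9 to 7.1). The contrast is 2.5 points. The lower limit is 2.5 − √(2.7² + 4.6²) = −2.8 and the upper limit is 2.5 + √(5.5² + 1.6²) = 8.2.

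| Events, intervention vs control (of 120 each) | Risk difference, points | 95% CI, clustering ignored | 95% CI, design effect 1.575 |
|---|---|---|---|
| 0 vs 0 | 0.0 | −3.1 to 3.1 | −4.8 to 4.8 |
| 2 vs 1 | 0.8 | −3.1 to 5.1 | −4.8 to 6.8 |
| 6 vs 3 | 2.5 | −2.8 to 8.2 | −4.6 to 10.1 |
| 12 vs 6 | 5.0 | −1.9 to 12.2 | −3.9 to 14.3 |

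**What the change cannot do.** Ignoring clustering, the power at 120 per arm to detect a doubled risk is 9%, 15%, 31%, 58% and 93% for control risks of 1%, 2%, 5%, 10% and 20%. Clustering lowers these. Reporting the difference does not alter them.

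**The case against.** A reader might infer that safety as a whole has no between-arm comparison. The document does not support that. The score named as the safety outcome is compared between arms, and SIDAS and K-6, which cover the more plausible harms, are modelled between arms. The gap is confined to events.

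A reader might also infer that the trial could not say whether the workshop causes harm. That goes too far. Both arms' percentages will be reported, so a crude difference can be derived. Suicide attempts and suicides also get a psychiatrist's assessment of a possible link to the intervention. For rare events the main limit is sample size, which the change does not remove. What remains is that a cluster-aware interval for the difference cannot be recovered from two separate per-arm intervals. The case review covers suicide attempts and suicides but not other AEs, and it takes place in an open-label trial.

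A tempting illustration is 51 against 36 events of 120. The separate Wilson intervals overlap (34.0 to 51.4% and 22.5 to 38.7%), while the unadjusted difference of 12.5 points has an interval of 0.3 to 24.2. It does not carry the point. The counts are invented, and with the design effect of 1.575 the interval is −2.7 to 26.9. An ICC of about 0.005 is enough for it to reach zero.

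The two safety passages could also be read as using different units, events in one and participants in the other. The Safety outcomes subsection settles this: "Proportions of participants with the respective (S)AEs will be reported".

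Finally, the safety aim is exploratory, and a difference column could be added in the SAP without contradicting the article. Both are fair, and they keep the point modest. Still, the Safety subsection states a choice and a reason for it, and the reason supports leaving out the test but not the estimate.

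**Conclusion.** The point holds for SAEs, suicide attempts, suicides and other AEs: the plan names no between-arm estimate, and the rarity of events does not justify that. It is a cheap improvement in analysis and reporting, not a flaw that invalidates the safety assessment.

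Its size is best seen at zero events. With 120 per arm, an excess of about 3 points would remain compatible with the data if clustering is ignored, and about 4.8 points under the primary outcome's design effect. These figures assume equal arms and complete event follow-up, and the second also assumes that the ICC of 0.05 carries over to events.

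Nothing in the document says that per-arm intervals will be compared by eye or that zero events will be called safe. The abstract states an expectation, not a decision rule.

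**What to change.** In the Safety subsection, for any SAE, suicide attempt, any AE and each named AE, report:
- the number and percentage of participants with at least one event in each arm;
- the risk difference, intervention minus control, with a 95% CI that allows for the randomised groups, and no p-value. Name the interval method in advance, including what will be used if counts are too small for a model.

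Suicides are included under any SAE and stay listed by arm. Use the same risk difference for the event outcomes in the subgroup section. State that the safety conclusion will be limited to the excess that the interval excludes, and note in advance that no events in 120 per arm would leave about 3 points open before clustering is allowed for.

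The cost is a few lines of text and one table column, with no new data. The downside is that the intervals will be wide and look less reassuring, and precision for rare events does not improve.
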